## Abstract

**Introduction::**

This study aims to compare clinical effect between Jade moxibustion and traditional moxibustion, and to determine the clinical effect of Jade moxibustion on knee osteoarthritis (KOA).

**Methods/Design::**

This is a 2-parallel-group, randomized controlled trial. A total of 148 subjects with KOA (Kellgren–Lawrence grade II or III) will be recruited and randomized to receive Jade moxibustion treatment or a traditional moxibustion treatment in a 1:1 ratio. Jade moxibustion group: The affected knee of the subjects will be covered with jade kneepad. Traditional moxibustion group: Chosen the ST35, ST34, EX-LE4, SP10 and Ashi points at the affected knee. The subjects will receive treatment three times a week, altogether 12 times in 4 weeks. The main outcomes are WOMAC knee pain score, knee function score and SF-36 quality of life questionnaire changes at the 4th week. Secondary outcomes include WOMAC knee pain score and knee function score, overall clinical efficacy evaluation, medication, safety evaluation at the 2nd, 12th, and 24th week, and cytokines related to osteoarthritis in serum.

**Discussion::**

This randomized controlled trial used traditional moxibustion as a control group to provide rigorous evidence for the clinical efficacy and safety of Jade moxibustion in treatment of KOA.

**Trial Registration::**

ISRCTN registry, No 21174552. Registered on 28 February 2020.

## Introduction

1

Knee osteoarthritis (KOA) is a common cause of disability in the elderly.^[1]^ In the USA, 12.1% people over 60 years of age suffered knee OA.^[2–4]^ The risk of KOA increases by age.^[5]^ The incidence of KOA is 30% in China, which women have higher risk than men.^[6,7]^ There is a correlation between knee pain and mortality in obese people. Mortality can be reduced by effective intervention, reduction of knee pain and prevention of complication.^[8]^

Nearly 23% of osteoarthritis patients with knee or hip joint suffer from neuropathic pain.^[9]^ The goals of the treatment of KOA is to reduce symptoms and ultimately slow disease progression, which may improve the quality of life and activity of subjects.^[10]^ Therefore, it is very urgent and important to find alternative and complementary methods to treat and control inflammatory pain. At present, NSAID and intraarticular corticosteroid are commonly used to relieve the pain of symptomatic osteoarthritis of the knee. NSAID has renal toxicity, serious gastrointestinal complications and cardiovascular events,^[11]^ while intraarticular corticosteroid has potential harmful effects on the knee cartilage, although both of them are helpful to relieve the pain.^[12]^

Moxibustion is a traditional Chinese medicine (TCM) method of the treatment of KOA. Unlike drug treatment, moxibustion rarely causes side effects, which can effectively relieve the pain symptoms of KOA patients,^[13–15]^ and improve the overall function.^[16–18]^ In a meta-analysis of a randomized controlled trial involving 11 moxibustion treatments for KOA, the moxibustion group had significantly improved overall pain and physical function scores compared to the traditional oral medication.^[19]^ Another study indicates that real moxibustion had effect on the osteoarthritis pain as compared to sham moxibustion.^[20]^

There have been records of using jade for treatment since ancient times in China. Inlaid in the inner side of the kneepad, the temperature of the kneepad can reach 43 to 47°C after being electrified. The results show that transient receptor potential vanilloid 1 (TRPV1) is related to the anti-inflammatory effect of the body.^[21]^ Jade moxibustion is to wrap the jade kneepad around the knee joint, which is easy to operate and can adjust the temperature. However, the therapeutic effect of Jade moxibustion on KOA has not been evaluated in clinical trials. The hypothesis is that 3 sessions per week of Jade moxibustion will have the clinical effect on KOA.

## Method

2

### Study design

2.1

This trial is a non-inferiority randomized controlled clinical trial, which is designed to compare the clinical efficacy of the Jade moxibustion and traditional moxibustion in treating typical inflammatory pain–KOA. The protocol has been registered on ISRCTN registry (No 21174552) and will be conducted in accordance with the Declaration of Helsinki.

The study flow outline is shown in Figure 1

**Figure 1 F1:**
[figure not shown]
Study flow chart.

### Study setting, recruitment, and ethics

2.2

Recruitment will be carried out in Tongren Hospital Affiliated to Shanghai Jiaotong University and Shanghai Pudong Hospital of Traditional Chinese Medicine. A total of 148 subjects with KOA will be enrolled. The study was approved by the medical ethics review committees of Tongren Hospital (No. Tongren 2019-022-02). Recruitment will be carried out through social platform, out-patient department, community propaganda and other ways. Investigator will contact people who are willing to participate in the study by telephone, conduct preliminary screening according to the inclusion and exclusion criteria, and then, if appropriate, arrange the acupuncture specialist for face-to-face baseline visit at an appropriate time, meanwhile the subjects will receive radiographic evaluation. The investigator will introduce the research protocol (i.e., the research purpose, procedures and time commitment and potential risks and benefits related to the research) in detail to potential subjects and obtain written informed consent. The subjects’ privacy information will be protected. Each subject will be given a unique random number as a direct identifier of the case report.

### Inclusion criteria

2.3

1.Age 50 to 75 years old.2.According to the American College of Rheumatology Diagnostic Criteria for KOA.^[22–26]^3.Radiologic confirmation of KOA (Kallgren-Lawrence level ≥1).^[27]^4.Moderate or greater knee pain on most days of the past month; the subject's visual analog scale baseline score for arthritic pain is 40 points and above.5.Agreed to be randomly assigned, understand and would like to sign an informed consent.

### Exclusion criteria

2.4

1.Knee pain caused by other diseases (such as rheumatoid arthritis, fibromyalgia syndrome, chronic fatigue syndrome and ankylosing spondylitis).2.Treatment of steroid drugs in the past 3 months.3.History of receiving acupuncture/moxibustion treatment within 3 months.4.Intra-articular injection of hyaluronate over the past 6 months.5.History of joint puncture or arthroscopy in the past year.6.History of the knee/hip replacement surgery or planning to perform such surgery during the trial.7.Use of other topical treatments, such as topical use of drugs.8.Presence of any serious diseases including heart disease, lung disease, kidney disease, liver disease or malignant tumor, systemic infection or infectious disease and mental illness.9.Participation in another clinical study in the past 1 month.

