### Randomization

2.6

A total of 148 subjects with KOA who are eligible per protocol will be randomly assigned to group A - Jade moxibustion group or group B - traditional moxibustion group in a 1:1 ratio. The subject will first receive a brief phone consultation, after that, the subject will be allocated to the site. After the investigator and the subject signed the informed consent, the investigator will perform a simple rheumatic examination. The investigator will make a diagnosis based on the knee x-ray film brought by the subject or the knee X-ray performed at site. Only the subject who meet the inclusion/exclusion criteria will be randomized by central network randomization program. Then investigator will make baseline assessment and arrange treatment.

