### Interventions

2.8

The treatment plan of the trial is based on the traditional moxibustion in the clinical treatment of KOA, combined with the characteristics of Jade moxibustion instrument itself, considering the standardized requirements of the trial design.

According to the literature review, the following 5 acupoints are selected for each treatment.ST35, ST34, EX-LE4, SP10, and Ashi point (i.e., tender point around the knee joint) are all located in the knee region, and they are common acupoints in the global clinical research of treating KOA.^[28]^ In anatomy, Acupuncture point ST35 and EX-LE4 are located close to the thinnest part of the knee joint, so the thermal effect of moxibustion and Jade moxibustion can directly reach the articular cavity. According to the biomechanical study, most of the clinical diagnosis and treatment guidelines of KOA pay special attention to the muscle strength training of quadriceps femoris.^[29–32]^ The muscle strength of extensor and flexor groups of knee joint is closely related to the symptoms of KOA.^[33]^ SP10 and ST34 are near the area of vastus medialis obliquus and lateral great respectively, so they may directly improve the state of quadriceps femoris. Ashi point is the most painful point according to the actual situation of the subjects.

Subjects are allowed to take concomitant medication, but we will encourage them not to change their medications during the trial. At the same time, other therapies are not allowed, such as acupuncture, sodium hyaluronate injection.

The treatment process will be supervised throughout by the staff of the research team. The two groups of subjects will be treated separately by the rigorously trained treatment operator.

Jade moxibustion Group

The Jade Moxibustion group will use the HX001 temperature-controlled energy knee pads produced by Jiaxing Fuqiduo Thermal Bed Co., Ltd. Jade kneecap will be electrified and preheated for 3 minutes until the temperature rises to 46°C, press the jade in the kneecap against the knee which can be fixed on the knee of the subject. If the patients felt burning at the skin, the temperature will be adjusted.

Traditional moxibustion group

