The traditional moxibustion group will use stick-on moxa cone produced by Nanyang Hanyi Moxibustion Co., Ltd. The stick-on moxa cone will be ignited after being attached to the acupoints. When the patients felt burning at the skin, the moxa cone will be removed and a new one would be attached and ignited again. A small pillow will be placed in the popliteal fossa and keep the knee slightly bent and stick moxa cone on the acupoints of the subjects.

Treatment of 2 groups will last for 20 minutes, 3 times a week and altogether 12 times in 4 weeks (every Tuesday, Thursday, and Saturday). If the subject is unable to receive treatment on time, he or she will be required to complete the treatment within that week. If any adverse event occurs, treatment will be suspended, and the investigator can decide whether to terminate the treatment.

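### The in-session rule for easing heat depends on the patient feeling burning, but no eligibility criterion requires intact heat or pain sensation at the knee

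*Protocol article*

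**What the plan says.** **Eligibility.** Sections 2.3 and 2.4 give 5 inclusion and 9 exclusion criteria as numbered lists. Section 2.6 makes them the entry gate: "Only the subject who meet the inclusion/exclusion criteria will be randomized by central network randomization program". Three criteria come nearest to this point:

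- Inclusion 4: "Moderate or greater knee pain on most days of the past month", with a minimum baseline visual analog score for arthritic pain.
- Exclusion 7: "Use of other topical treatments, such as topical use of drugs".
- Exclusion 8: "Presence of any serious diseases including heart disease, lung disease, kidney disease, liver disease or malignant tumor, systemic infection or infectious disease", and mental illness.

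**Contact before randomisation.** After telephone screening, section 2.2 has the investigator "arrange the acupuncture specialist for face-to-face baseline visit at an appropriate time". Under section 2.6, once consent is signed, "the investigator will perform a simple rheumatic examination".

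**Heat rule in each arm (section 2.8).** Jade arm: "If the patients felt burning at the skin, the temperature will be adjusted". Traditional arm: "When the patients felt burning at the skin, the moxa cone will be removed", after which a fresh cone is lit.

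**Other safeguards.** The Jade pad is a temperature-controlled device with a working range of 43 to 47°C (Introduction) and a preheating target of 46°C (section 2.8). Section 2.8 also provides trained operators, staff supervision of all treatment, and suspension of treatment on any adverse event. Section 3.2 requires subject and investigator to report adverse events at every treatment or visit, lists redness and blisters as side effects in both arms, and asks after each session what the subject felt, with an answer option for feeling nothing.

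**The concern.** A heat rule that is triggered by the patient's sensation works only if the patient can feel heat or pain in the skin of the knee. The entry criteria do not ask for this. A site that follows the published list as written could randomise someone with known sensory loss at the knee, for whom the stated trigger may come late or not at all. What is at stake is the safety of individual participants over up to 12 sessions of 20 minutes. The article itself expects skin injury: section 3.2 names blisters, and section 2.5 mentions serious infection after blistering as an example of a major problem.

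**Working it through.** No sample size, power or alpha figure bears on this point, so the check is a count of criteria and a side-by-side reading.

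**Step 1. Count the criteria (sections 2.3 and 2.4).**

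- Inclusion, 5: age; clinical diagnosis; radiographic grade; pain level; agreement to randomisation and consent.
- Exclusion, 9: other causes of knee pain; steroids; recent acupuncture or moxibustion; hyaluronate injection; joint puncture or arthroscopy; joint replacement; topical treatment; serious disease; another study.
- Total: 5 + 9 = 14.
- Criteria naming heat or pain sensation at the knee: 0 of 14.
- Criteria naming skin condition in the treatment area: 0 of 14.
- Criteria that could catch some such patients without requiring it for all: 2 of 14 (exclusions 7 and 8). Exclusion 7 removes users of a topical treatment, so untreated skin disease passes. Exclusion 8 is open-ended, but mild sensory loss or a local skin lesion need not count as a serious disease.

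Inclusion 4 makes a knee with no pain perception unlikely. It concerns arthritic pain, however, and does not establish that the overlying skin senses heat.

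**Step 2. Count the stated triggers for easing heat before an adverse event (section 2.8).** There is one in each arm, and in both it is the patient feeling burning.

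**Step 3. Ask of each safeguard when it acts and whether it keeps such a patient out.**

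| Safeguard | Section | When it acts | Depends on sensation? | Requires exclusion before session 1? |
|---|---|---|---|---|
| Face-to-face specialist visit | 2.2 | Before randomisation | No | No, as no criterion directs it |
| Simple rheumatic examination | 2.6 | Before randomisation | No | No, for the same reason |
| Temperature-controlled pad (Jade arm only) | Introduction, 2.8 | During session | No for the device range; yes for the stated reason to adjust | No |
| Trained operators, supervision | 2.8 | During session | No, but no heat-easing rule is attached | No |
| Suspension on adverse event | 2.8 | Once an event has occurred | No | No |
| Adverse-event reporting, redness and blisters listed | 3.2 | At each treatment or visit | No | No |
| Question on what was felt | 3.2 | After each session | It asks about sensation | No, and no action follows from the answer |

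The last row can identify a patient who feels nothing after session 1, with 12 − 1 = 11 sessions still to come. That is useful, but the first exposure has already taken place.

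**Step 4. Size.** The article gives no prevalence of impaired heat sensation and no burn rate, so no number of affected patients is derived.

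**The case against.** The strongest reply is that heat control does not rest on the patient alone. Suspension on any adverse event stops heat altogether and needs no report from the patient. Redness is visible and heads the list of side effects, so if it counts as an adverse event, supervising staff have a reason to stop before a blister forms. The sensation question after each session goes directly to the gap. The Jade device has its own temperature control. All of this stands. A reader might infer that nothing in the plan except the patient's feeling can stop the heat, and section 2.8 read with section 3.2 contradicts that inference. What remains is timing: these measures act once heat has been applied, or lead to no stated action.

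A second reply is that a journal article condenses, and a fuller protocol could hold further contraindications. That limits confidence. It does not remove the point, because the eligibility criteria are printed as numbered lists and section 2.6 makes meeting them the condition for randomisation.

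A third reply is that the skin half is a preference. In part this stands. A patient with damaged skin can still feel burning, so the skin question does not follow from the heat rule. The remarks on blisters and infection in sections 2.5 and 3.2 concern harm caused by treatment, not heating of skin that is already damaged. The skin item is therefore secondary.

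A reader might also take the Introduction's figure of nearly 23% with neuropathic pain as the share at risk. That figure describes a type of pain in knee or hip osteoarthritis, not loss of heat sensation in the skin, and it cannot be used in that way.

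**Conclusion.** The point holds as a minor safety gap in who may be enrolled. In both arms the stated rule for easing heat before an adverse event presumes sensation that 0 of the 14 entry criteria require, and no stated safeguard excludes such a patient before the first session.

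This rests on two assumptions: that the published list is the list sites apply, and that specialist judgement at the visit is not bound by an unpublished contraindication list. If a fuller protocol already contains the exclusion, the point falls away.

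The documents do not support a claim that burns are likely, that the 46°C setting is unsafe, or that the comparison between arms is biased.

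**What to change.** Add one exclusion to section 2.4: known impaired heat or pain sensation at the knee (for example, peripheral neuropathy). It would be judged from history at the face-to-face visit in section 2.2.

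As a separate local-suitability item, the same line can exclude broken, infected or diseased skin in the treatment area, judged by inspection at that visit.

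No new test, visit, temperature limit or session rule is needed. The cost is one line of text and a slightly smaller eligible pool.

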### Withdrawal criteria

2.5

Subjects who drop or discontinue prior to completion of the treatment period should conduct a questionnaire survey and those who have serious adverse reactions will be reported to the ethics committee.

1.Those who have not completed the treatment and have withdrawn before the end of treatment.2.Any serious adverse reactions.3.Major problems in the protocol design or trial process (such as those who are seriously infected due to blistering).

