### Primary outcome indicators

3.1

The primary outcome measure is the change in pain relative to baseline at the Western Ontario and McMaster Universities Osteoarthritis Index (WOMAC) in 4 weeks. The most painful knee joint for the subject will be recorded at the baseline, which will be the joint we measured throughout the trial. We will also measure WOMAC pain at week 2, 8, 12, and 24.

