### Secondary outcome indicators

3.2

The most important secondary outcome measurement is the improvement of WOMAC function in week 4. We will also assess the total score, function score and stiffness score of WOMAC at baseline, weeks 2, 8, 12, and 24. Visual analog scale pain score will be used to evaluate the arthritis pain of subjects at baseline, weeks 2,4, 8, 12, 24. SF-36 will be used to measure the quality of life of the subjects in the 4th, 12th, and 24th week. In addition, we will evaluate the efficacy of a 5-point scale in the fourth week (1 = very poor, 2 = poor, 3 = general, 4 = OK, 5 = very good.).

Any adverse event, whether related to treatment, requires the subject and investigator to report on each treatment or visit. Side effects include redness and blisters by Jade moxibustion and traditional moxibustion. Serious adverse events will be reported to the Ethics Committee. During the follow-up period (week 5 to week 24), we will call the subject weekly to find out about the adverse reactions and side effects that may occur during the week.

After 4 weeks of treatment, investigator will ask the subjects about the safety of the treatment: safe, fewer safe, have safety problem, and have serious safety problem. After each treatment we will ask the subject's feeling: “What do you feel during the treatment? 1. Heat; 2. Cold; 3. Pain; 4. no feeling; 5. Other, please describe”

The subjects will be allowed to take the analgesic or non-steroidal anti-inflammatory drugs used before the test, we will ask subjects to record the daily dose during the entire clinical trial, and then analyze the changes in the dose.

We will measure the outcome of the baseline, week 2, 4, 8, and 12 at the hospital. For the outcome of Week 24, we will mail the questionnaire to the subjects and ask them to post them back after filling them out.

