### Statistical analysis

3.6

Intention-to-treat analysis is the principle of this study, which includes all subjects in the designated treatment group, as well as subjects who have completed at least one course of treatment. The significant difference level is set to 0.05. The baseline characteristics of subjects will be summarized in both groups. For continuous results, the normal distribution of the data is labeled as the mean (standard deviation). For the main outcome, the remission rate of the fourth week will be calculated and χ^2^ test will be used to compare the Jade moxibustion group with the traditional moxibustion group. For secondary outcomes, unpaired scores including WOMAC pain, functional and stiffness scores, SF-36, expectation and reliability of treatment, and overall treatment outcome will be compared at all follow-up time points in both groups. T-test or Wilcoxon rank sum test will be used to compare continuous variables. We will use SPSS version 22 (IBM SPSS Statistics, NY) for statistical analysis.

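### Section 2.5 does not separate stopping treatment from leaving follow-up, so the week-4 WOMAC needed for the intention-to-treat analysis is not secured for patients who stop early

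*Protocol article*

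**What the plan says.** Five parts of the protocol article bear on this.

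- **Section 2.5 (Withdrawal criteria).** The opening sentence puts dropping out and discontinuing together and asks the same of both: "Subjects who drop or discontinue prior to completion of the treatment period should conduct a questionnaire survey". The list that follows includes "Those who have not completed the treatment and have withdrawn before the end of treatment" and "Any serious adverse reactions". A third item covers major problems in the design or conduct of the trial, with serious infection after blistering as its example.
- **Section 2.8 (Interventions).** Treatment is given "3 times a week and altogether 12 times in 4 weeks". After an adverse event, "treatment will be suspended, and the investigator can decide whether to terminate the treatment". This concerns treatment only; follow-up is not mentioned.
- **Sections 3.1 and 3.2 (Outcomes).** "The primary outcome measure is the change in pain relative to baseline", on WOMAC at 4 weeks. On visits: "We will measure the outcome of the baseline, week 2, 4, 8, and 12 at the hospital". Week 24 is by mailed questionnaire, and weekly telephone calls run from week 5 to week 24. No exception is stated for patients who have stopped treatment.
- **Section 3.5 (Sample size).** The size is raised to 74 per group to allow for a preset 10% shedding. The section also reports no shedding in the previous trial.
- **Section 3.6 (Statistical analysis).** "Intention-to-treat analysis is the principle of this study, which includes all subjects in the designated treatment group". The sentence then adds subjects who completed at least one course of treatment. The main comparison is a χ² test of week-4 remission rates.

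**The concern.** Stopping treatment and leaving the trial are different events. An intention-to-treat analysis needs the outcome of patients who stop treatment as much as that of patients who finish. Section 2.5 handles both under one heading and names only an unspecified survey, so a site could reasonably take a patient who stops as withdrawn and not arrange the week-4 assessment. A form filled in on the day of stopping would not be a week-4 value.

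Such losses are unlikely to be random. Section 3.2 names redness and blisters as side effects of both treatments, and heat is handled differently by arm: the pad's temperature is adjusted, while the moxa cone is removed and replaced. Stopping may therefore depend on arm, and it may also depend on lack of effect. In a non-inferiority trial, loss related to both arm and outcome can distort the result, and no later analysis plan can recover a week-4 score that was never collected.

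**Working it through.** **1. The passages side by side.** Section 2.8 fixes a four-week treatment period and section 3.1 fixes the primary outcome at four weeks, so every early stopper stops before the primary time point. Section 3.2 schedules week 4 without exception, which favours continued collection. Section 2.5 calls the same patients withdrawn and names a survey without instrument or date, which leaves collection open. Section 3.5 inflates the sample for shedding, so shed patients are expected to be missing from the effective sample. Section 3.6 wants everyone. No sentence settles the matter.

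**2. How many patients.** Section 3.5: 67 × 1.10 = 73.7, rounded up to 74 per group. The allowance is 74 − 67 = 7 per arm (10% of 148 is about 15 in all).

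**3. Effect on the estimated difference.** Inputs from section 3.5: response rates of 55.56% (Jade) and 46.51% (traditional), a difference of 9.05 points. Assume that these are the rates among patients with data, that 7 of 74 are missing in the arm or arms named, and that all those missing are non-responders. The full-arm rate is then the observed rate × 67/74.

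- Jade: 55.56% × 67/74 = 50.3%
- Traditional: 46.51% × 67/74 = 42.1%

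| Where the loss falls | Full-arm difference | Error in the observed 9.05 points |
|---|---|---|
| Jade only | 50.3 − 46.5 = 3.8 | 5.3 too high |
| Traditional only | 55.6 − 42.1 = 13.4 (unrounded inputs) | 4.4 too low |
| Both equally | 50.3 − 42.1 = 8.2 | 0.9 too high |

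With no assumption on the missing responses (7/74 = 9.5 points per arm), the full-arm difference lies between 8.2 − 9.5 = −1.3 and 8.2 + 9.5 = +17.7 points. At exactly 10% missing the range is −1.9 to +18.1.

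**4. Effect on a false claim of non-inferiority.** This needs a margin on the response-rate scale. The printed cutoff of 0.5 cannot serve: (1.96 + 0.8416)² × (0.2488 + 0.2469) / (0.5 + 0.0905)² = 11.2, or 12 per group, not 67. A margin of 0.15 gives 7.849 × 0.4957 / 0.2405² = 67.3, or 68, close to the stated 67. I therefore **assume** 0.15.

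Put the truth at the margin: traditional 46.51%, Jade 31.51%. Dropping 7 non-responders turns a true rate p into p × 74/67. With d the observed difference, P(false claim) = Φ((d + 0.15)/SE − 1.96).

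| Loss | Jade rate (n) | Traditional rate (n) | d | SE | P(false claim) |
|---|---|---|---|---|---|
| Traditional only | 31.5% (74) | 51.4% (67) | −0.199 | 0.0815 | 0.5% |
| Both equally | 34.8% (67) | 51.4% (67) | −0.166 | 0.0844 | 1.6% |
| Jade only | 34.8% (67) | 46.5% (74) | −0.117 | 0.0821 | 5.9% |

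The nominal level is 2.5%. Only loss confined to the Jade arm raises it.

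**The case against.** The strongest case on the other side is that section 2.5 is merely terse. A reader might infer that early stoppers give an exit questionnaire and nothing more, that week-4 WOMAC is not collected from them, and that intention-to-treat therefore cannot be carried out. The document supports none of these three steps.

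- The survey is not described as an exit form or as the only data. WOMAC is itself a questionnaire, and section 3.2 uses that word for the mailed week-24 outcome forms. The survey could be the outcome instrument.
- Section 3.2 schedules week 4 with no exception, and section 2.8 speaks of ending treatment, not participation. The first withdrawal item joins non-completion with having withdrawn, so it need not equate the two.
- All randomised patients can still be analysed by imputation or by counting missing patients as non-responders. Such rules may stand in a full protocol or analysis plan that is not shown. The data collection timetable (Table 1) is not visible either.

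The size is also easily overstated. Carrying a 5-point shift in Jade's favour into the non-inferiority test gives a false-claim rate of about 8.5%. That shift is taken at the pilot Jade rate of 55.6%; at the margin the Jade rate is 31.5%, and the same loss inflates it by only 34.8 − 31.5 = 3.3 points. If moxa cones caused more stopping, the loss would fall on the control arm and, with non-responders lost, would work against Jade. The previous trial had no dropout.

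All of this stands, and it limits the point to data that are not secured. It does not remove the point: section 2.5 states a rule, and that rule leaves the week-4 assessment of these patients open.

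**Conclusion.** The point holds in a limited form. Section 2.5 makes non-completion and any serious adverse reaction withdrawal criteria, does not separate stopping treatment from leaving follow-up, and names only an unspecified survey. Week-4 WOMAC is therefore not secured for these patients, although section 3.6 relies on it.

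About 7 of 74 per arm could be affected if shedding reaches the preset 10% and all of it is early stopping without week-4 data. Both are assumptions, and the earlier trial suggests fewer. Under the further assumption that all those lost are non-responders, the error in the difference runs from 5.3 points too high to 4.4 points too low, and is under 1 point if loss is equal. With an assumed margin of 0.15, the false-claim rate runs from 0.5% to 5.9% according to which arm loses patients. The documents do not show which arm that would be, so no direction can be claimed. This is a cheap improvement to the wording, not a flaw that defeats the trial.

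**What to change.** Reconcile sections 2.5, 2.8, 3.2 and 3.6 with wording such as: *Patients who stop treatment for any reason remain in follow-up. WOMAC is collected at week 4 and at the later scheduled visits, by mail or telephone if they cannot attend, unless they withdraw consent to follow-up. All randomised patients are analysed in the group to which they were assigned.* Section 2.5 should also say which instrument the survey is and when it is completed, and should record withdrawal from treatment and withdrawal of consent to follow-up as separate events.

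This concerns data collection only and leaves the rules for suspending or ending treatment as they are. The cost is the wording and a few extra questionnaires, for about 7 patients per arm at the preset rate. Mailing at week 24 and weekly calls from week 5 are already planned; mail or telephone contact at week 4 would be new for those who cannot attend.
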